### Sample size calculation

The primary analysis will consist of two baseline adjusted comparisons of PR prevalence after twelve months, each comparing one of both intervention groups with the control group.

A Bonferroni adjustment for testing two times will be applied, yielding a significance level of α = 0.05/2 = 0.025. The unit of observation in the primary analysis is the home (= cluster).

It is assumed that prevalence throughout the homes will be approximately normal distributed. The estimation of the required sample size is based on the *t*-test comparing the prevalence differences between two groups (intervention and control) from baseline to twelve months. The power of each test in the primary analysis is estimated separately under the same circumstances.

Based on data of the initial study [1], a sample size of 38 homes per group is needed to detect a difference in prevalence of 5 % after twelve months with 90 % power (β = 0.10) using a two-sided significance level of 2.5 % (α = 0.025) and assuming a standard deviation of σ = 6.0 in both groups. Furthermore, presuming a dropout rate of 5 %, a sample size of 40 clusters per group, i.e. a total of 120 clusters, with a mean cluster size of 90 residents is planned.

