### Statistical analysis

Statistical analysis will follow the Good Clinical Practice (GCP) standards and will be conducted after the end of the follow-up by the blinded biostatistician (BH) in charge. Data analysis will be performed by intention to treat. In the primary analysis, the prevalence of restraints on both intervention groups will be compared to the control group on cluster level.

It is assumed that prevalence throughout the nursing homes will be approximately normal distributed.

The statistical tests will be adjusted for baseline prevalence by fitting a linear model with twelve-month prevalence of the clusters as the dependent variable and using baseline prevalence and two indicator variables of the intervention groups as the independent variables. Differences of prevalence changes between each intervention group and the control group will be estimated and statistically tested using contrasts of the model. Both tests will be performed using a two-sided level of significance of α = 2.5 %, which is adjusted for double testing by Bonferroni. Cluster adjustment will be ensured by using clusters as observation units. Based on the same linear model, a secondary analysis will estimate the contrast between the prevalence differences of both intervention groups. This result will be interpreted in a descriptive manner. A non-significant difference cannot be interpreted as the equivalence of both interventions. Possible equivalence tests do not reach enough power to get reasonable results.

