Data will be described at all three measurement points (T_0_, T_1_, T_2_), stratified by treatment groups using frequency tables, means, standard deviations, percentiles and prevalence, depending on the distribution of the variables. Data on the residents will be described according to the resident level. Variances and confidence intervals of the outcomes of residents will be estimated cluster-adjusted using the intra-class correlation coefficient (ICCC) [37]. In a further secondary analysis, the time courses of the prevalence in the three groups will be investigated on resident level, adjusting for clusters and for repeated measurement. A generalized linear mixed model is fitted with binary dependent variable “application of PR”. Fixed effects are treatment group, time, interaction of treatment and time, and the baseline value of PR. Cluster is a random effect, in a secondary model the interaction cluster*time is also included as a further random effect. Adjustment for repeated measurement is performed by covariance patterns [38], primarily assuming a compound symmetry structure. Other covariance structures and possible exclusion of the interaction between treatment and time will be discussed comparing different models.

Secondary outcomes (quality of life on a 10 %-subpopulation; falls and fall-related fractures) will be described at each time documented, and stratified by treatment groups. Variances and confidence intervals are cluster-adjusted using ICCC [37]. Statistical comparisons between the treatment groups will be performed using (generalized) linear mixed models as described above for the primary outcome adjusting for the clusters and the repeated measurements.

Missing values on cluster level would only occur in the case of dropout homes, which, it is assumed, will be very rare and improbable. It is assumed that the documentation of PR at each investigation time will be nearly complete, so that there is no relevant selection bias from the estimated prevalence of PR of each home. Furthermore, in the secondary analyses the mixed models use all the available values of the residents and do not exclude residents because of partially incomplete values. It is not planned to impute missing values. The level of significance is 5 %, if not stated otherwise (e.g. in the primary analysis). All of the tests are performed two-sided.

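### Both primary tests stay at 2.5% under single-step Bonferroni; Holm's step-down would give a modest, free gain in confirming both programmes (low severity, not an error)

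*Protocol article*

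**What the plan says.** The Sample size calculation section defines two primary comparisons, "each comparing one of both intervention groups with the control group". It then says "A Bonferroni adjustment for testing two times will be applied", "yielding a significance level of α = 0.05/2 = 0.025". The Statistical analysis section repeats the two-sided 2.5% level for both tests, "which is adjusted for double testing by Bonferroni", and closes with "All of the tests are performed two-sided". No step-down or ordered rule is given, and no reason for preferring the single-step form.

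The sample size uses the same level. It is set "to detect a difference in prevalence of 5 % after twelve months", with SD 6.0 and 90% power, giving 38 homes per group, or 40 after 5% dropout. The power target applies to each comparison on its own: "The power of each test in the primary analysis is estimated separately under the same circumstances". No power is stated for confirming both programmes.

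**The concern.** With a fixed 2.5% for each test, success in one comparison does nothing for the other. A programme with p = 0.03 fails even if the other has p = 0.001. Holm's procedure would declare both effective in that case, with the same guarantee on the family-wise error.

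The trial cares about both answers. The Discussion expects a reduction from both versions and envisages roll-out of the concise one if it succeeds. The Statistical analysis section makes the direct contrast between the two programmes descriptive and says that equivalence tests would lack power. Each version must therefore earn its own result against control, and any loss from the single-step rule falls on confirming the second programme.

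**Working it through.** **Inputs** (Sample size calculation section): difference 5 points, SD 6.0 at home level, two-sided α = 0.025 per test, 90% power per test, 38 homes per group before dropout and 40 after. Allocation is 1:1:1 (Randomisation section).

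**Step 1: the plan's own figure.** For the two-sample t-test the noncentrality is 5 / (6 × √(2/n)).
- n = 37: power 0.8997.
- n = 38: noncentrality 3.632, critical value 2.288 on 74 df, power 0.908.

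So 38 is the smallest n that reaches 90%, and 38 / 0.95 = 40. The plan's figures reproduce.

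**Step 2: Holm keeps the 5% error under any dependence.**
- Both programmes null: a false claim needs the smaller p-value ≤ 0.025, which has probability at most 0.025 + 0.025 = 0.05.
- One programme null: a false claim needs that programme's p-value ≤ 0.05, which has probability at most 0.05.
- Neither null: no false claim is possible.

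The shared control arm is therefore no obstacle. Whatever passes at 2.5% under Bonferroni also passes under Holm.

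**Step 3: power under the plan's assumptions.** Simulation with at least 1,000,000 replicates per scenario, three arms, shared control (correlation 0.5), pooled SD on 3n − 3 df. At n = 38 the critical values are 2.272 (2.5%) and 1.982 (5%). Both true effects are 5 points and SD is 6.

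| Homes per group | Quantity | Bonferroni | Holm |
|---|---|---|---|
| 38 | Both confirmed | 85.1% | 90.8% |
| 38 | Each test | 91.1% | 94.0% |
| 38 | At least one confirmed | 97.2% | 97.2% |
| 40 | Both confirmed | 87.3% | 92.4% |

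Check: per-test power is half of (at least one + both). Bonferroni: (97.2 + 85.1)/2 = 91.15. Holm: (97.2 + 90.8)/2 = 94.0. Both agree with the table to rounding.

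**Step 4: false claims** (38 homes, SD 6).
- Both programmes null: 4.6% family-wise under either rule.
- One effect of 5 points, the other null: the false-claim rate for the null programme is 2.5% under Bonferroni and 4.6% under Holm.

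**Step 5: sensitivity to the SD.** The SD of 6 belongs to a t-test on changes from baseline. The primary model instead adjusts for baseline prevalence, and its residual SD is generally no larger. The article gives no value, so 5.5 and 5 are assumptions. Probability of confirming both, Bonferroni then Holm:
- SD 5.5: 91.8% and 95.4% at 38 homes; 93.4% and 96.4% at 40.
- SD 5: 96.5% and 98.2% at 38 homes; 97.3% and 98.7% at 40.

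**Step 6: smaller effects** (also assumptions, 38 homes, SD 6). Effects of 4 and 4 points: 60.4% and 70.8%. Effects of 5 and 3 points: 45.4% and 56.7%.

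**The case against.** The strongest reply is that nothing here is wrong. Bonferroni is valid for two tests, both sections state it the same way, and the sample size is built on it. The protocol promises 90% power per test and gets about 91%. Power to confirm both is a target that the protocol never sets. All of this stands.

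Two further points stand. A fixed 2.5% gives each programme's claim its own protection. Under Holm, that protection weakens to about 4.6% for an ineffective programme when the other one works, and nearer 4.9% if the SD is 5. Also, 97.5% intervals match Bonferroni decisions exactly, whereas under Holm the second comparison can be declared significant while its 97.5% interval includes zero. Either would be a fair reason to keep Bonferroni, but the article offers neither.

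Two stronger readings are tempting and not supported. A reader might infer from the 85.1% that the trial misses its power target. It does not, because the 90% is stated per test. A reader might also infer that the planned situation, with both programmes effective, is where Bonferroni loses most. Under the plan's own assumptions the joint loss is 5.7 points. It is larger only with smaller or unequal effects that the document does not posit: the plan powers both tests under the same circumstances, and the Background section suggests that the less extensive version may do as well or better.

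**Conclusion.** The point holds as a cheap improvement of low severity. The plan's rule is valid, consistent and adequately powered on its stated criterion. Holm is never less powerful at the same 5% family-wise error. With 5 points and SD 6, it adds 90.8 − 85.1 = 5.7 points to the probability of confirming both programmes at 38 homes per group, and 92.4 − 87.3 = 5.1 points at 40. Per-test power at 38 rises by 94.0 − 91.1 = 2.9 points, and the chance of confirming at least one does not change. The gain rests on both programmes being effective and on the SD. With a residual SD of 5 it falls to 1.7 points at 38 homes and 1.4 at 40.

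**What to change.** Before unblinding, and as a documented change, replace the fixed rule in the Sample size calculation and Statistical analysis sections with Holm: test the smaller of the two p-values at two-sided 2.5% and, only if it is significant, the larger at two-sided 5%. Keep the sample size of 38 (40) homes per group, since the Bonferroni calculation remains a lower bound on power under Holm. Report 97.5% intervals for both contrasts, and say in advance that the test decision follows Holm and may differ from the interval for the second comparison.

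The cost is a few sentences and no additional homes. The sponsor should accept knowingly the two downsides: the possible mismatch between interval and decision, and the higher false-claim rate for one programme when only the other works. If the sponsor prefers to keep 2.5% for each claim, one sentence giving that reason would settle the point.

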### Statistical analysis

Statistical analysis will follow the Good Clinical Practice (GCP) standards and will be conducted after the end of the follow-up by the blinded biostatistician (BH) in charge. Data analysis will be performed by intention to treat. In the primary analysis, the prevalence of restraints on both intervention groups will be compared to the control group on cluster level.

It is assumed that prevalence throughout the nursing homes will be approximately normal distributed.

The statistical tests will be adjusted for baseline prevalence by fitting a linear model with twelve-month prevalence of the clusters as the dependent variable and using baseline prevalence and two indicator variables of the intervention groups as the independent variables. Differences of prevalence changes between each intervention group and the control group will be estimated and statistically tested using contrasts of the model. Both tests will be performed using a two-sided level of significance of α = 2.5 %, which is adjusted for double testing by Bonferroni. Cluster adjustment will be ensured by using clusters as observation units. Based on the same linear model, a secondary analysis will estimate the contrast between the prevalence differences of both intervention groups. This result will be interpreted in a descriptive manner. A non-significant difference cannot be interpreted as the equivalence of both interventions. Possible equivalence tests do not reach enough power to get reasonable results.

Data will be described at all three measurement points (T_0_, T_1_, T_2_), stratified by treatment groups using frequency tables, means, standard deviations, percentiles and prevalence, depending on the distribution of the variables. Data on the residents will be described according to the resident level. Variances and confidence intervals of the outcomes of residents will be estimated cluster-adjusted using the intra-class correlation coefficient (ICCC) [37]. In a further secondary analysis, the time courses of the prevalence in the three groups will be investigated on resident level, adjusting for clusters and for repeated measurement. A generalized linear mixed model is fitted with binary dependent variable “application of PR”. Fixed effects are treatment group, time, interaction of treatment and time, and the baseline value of PR. Cluster is a random effect, in a secondary model the interaction cluster*time is also included as a further random effect. Adjustment for repeated measurement is performed by covariance patterns [38], primarily assuming a compound symmetry structure. Other covariance structures and possible exclusion of the interaction between treatment and time will be discussed comparing different models.

Secondary outcomes (quality of life on a 10 %-subpopulation; falls and fall-related fractures) will be described at each time documented, and stratified by treatment groups. Variances and confidence intervals are cluster-adjusted using ICCC [37]. Statistical comparisons between the treatment groups will be performed using (generalized) linear mixed models as described above for the primary outcome adjusting for the clusters and the repeated measurements.

Missing values on cluster level would only occur in the case of dropout homes, which, it is assumed, will be very rare and improbable. It is assumed that the documentation of PR at each investigation time will be nearly complete, so that there is no relevant selection bias from the estimated prevalence of PR of each home. Furthermore, in the secondary analyses the mixed models use all the available values of the residents and do not exclude residents because of partially incomplete values. It is not planned to impute missing values. The level of significance is 5 %, if not stated otherwise (e.g. in the primary analysis). All of the tests are performed two-sided.

Focus groups will be analysed by content analysis [39]. Two independent research team members will identify initial themes describing comparable aspects or meanings. To abstract the content, all initial themes will be labelled with codes. Based on the codes, categories and sub-categories will be developed. Coding and analysis will be discussed constantly. Disagreements about the themes will be resolved in a discussion. The content will be summarised and narratively described.

For the health economics analysis, mean costs as well as cost differences between intervention and control groups will be calculated. Cluster-adjustment will be conducted. Sampling uncertainty (95 % confidence intervals) will be estimated using bootstrap procedure because cost data are usually skewed. Effects will be taken from the documented events. ICER will be estimated in terms of costs per resident with avoided PR. The non-parametric bootstrap method will be employed to generate confidence intervals around the ICER estimate derived from the study sample [40, 41]. Uncertainty surrounding the ICER will also be presented on the cost-effectiveness plane and as the cost-effectiveness acceptability curve [42, 43]. Besides statistical uncertainty (sampling variation) with regard to costs and effects, every economic evaluation may contain some degree of data imprecision (e.g. resource costs/prices), which should be accounted for. To handle this type of uncertainty, a sensitivity analysis will be employed. In the sensitivity analysis, (uncertain) parameter(s) of the base-case analysis will be varied to determine whether changes in these parameters influence the results. We will report both, the revised point estimates and revised confidence intervals for costs, effectiveness, and cost- effectiveness that result from the sensitivity analyses.

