### Randomisation

Interventions will be implemented at the institutional level. Therefore, randomisation will be performed on a cluster level. Clusters will be allocated 1:1:1 between intervention and control arms. For the random assignment, computer-generated lists will be used with blocks of six, nine, and twelve nursing homes. The randomisation list will be generated by an independent external biometrician (BH). Because regional differences may influence the outcomes, randomisation will be stratified by region (Lübeck, Halle (Saale), Hamburg, and Witten). Allocation concealment will be ensured through assignment by an external independent researcher, who will inform the clusters about group allocation.

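### Randomisation is stratified by region, but the primary model omits region, so its standard error may be somewhat too large and its test conservative; the size is unknown and may be small

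*Protocol article*

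**What the plan says.** Under Randomisation, the protocol article gives both the design choice and its reason: "Because regional differences may influence the outcomes, randomisation will be stratified by region". The strata are Lübeck, Halle (Saale), Hamburg and Witten, with blocks of six, nine and twelve homes. Participants and recruitment plans about 30 clusters per region.

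Under Statistical analysis, the primary model regresses each home's twelve-month prevalence "using baseline prevalence and two indicator variables of the intervention groups as the independent variables". The same section specifies the resident-level mixed model: "Fixed effects are treatment group, time, interaction of treatment and time, and the baseline value of PR", with cluster as a random effect. The comparisons of secondary outcomes refer back to models of that kind. Region appears in none of these specifications, no reason is given for leaving it out, and no region-adjusted sensitivity analysis is planned.

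**The concern.** Blocked allocation within region balances the arms within each region. Differences between regions then largely cancel out of the treatment contrast, so the estimate varies less from one randomisation to the next. A model without region does not see this. It leaves the between-region variance in the residual and reports a standard error for a less precise design than the one used.

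At stake are confidence intervals wider than they need be, a test that runs below its stated level (already halved to 2.5% by Bonferroni), and some power. This is not a detail left to an analysis plan. The article lists the covariates of the confirmatory model, so an analysis plan that follows it omits region and one that includes region departs from the published model.

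**Working it through.** **Inputs from the article (Sample size calculation).** The design aims "to detect a difference in prevalence of 5 % after twelve months", "assuming a standard deviation of σ = 6.0 in both groups", with two-sided α = 0.025 per comparison, 90% power and the home as unit of analysis.

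**Reproducing the planned size.** The normal approximation gives 2 × (2.2414 + 1.2816)² × 6² / 5² = 35.7, i.e. 36 per group. The noncentral t-test gives power 0.8997 at 37 and 0.908 at 38, so 38 per group is right. 38 / 0.95 = 40 is right as well.

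**Assumptions.** R is the share of the cluster-level residual variance, after baseline prevalence, that region explains. The article does not give it, so 1, 5, 10 and 20% are shown. The SD of 6.0 stands in for the residual SD of the primary model. The formulas assume exact balance within regions.

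**Formulas, n = 38 per group, three groups.**

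- Standard error reported without region: 6 × √(2/38) = 1.376.
- True SD of the estimate, and standard error with region: 1.376 × √(1 − R).
- Overstatement: 1/√(1 − R) − 1.
- True level without region: 2 × [1 − Φ(2.2414/√(1 − R))].
- Power with region: noncentral t, noncentrality 5/[1.376√(1 − R)], 3 × 38 − 7 = 107 df, critical value 2.273.
- Power without region: same noncentrality, 3 × 38 − 4 = 110 df, critical value 2.272/√(1 − R). The estimate has the smaller true SD but is divided by the larger standard error.

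| R | True SD | SE overstated | True level | Power without region | Power with region | Gain (points) |
|---|---|---|---|---|---|---|
| 1% | 1.370 | 0.5% | 2.4% | 91.2% | 91.4% | 0.1 to 0.2 |
| 5% | 1.342 | 2.6% | 2.15% | 91.7% | 92.5% | about 0.8 |
| 10% | 1.306 | 5.4% | 1.8% | 92.2% | 93.9% | about 1.6 |
| 20% | 1.231 | 11.8% | 1.2% | 93.4% | 96.2% | about 2.8 |

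The powers without region are approximate to about 0.1 point. At R = 0, power is 91.14% without region and 91.12% with it, so the three extra terms cost about 0.02 points.

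**Simulation of the planned design** (120 homes, four regions of 30, blocks of 6, 9 and 12, so that incomplete blocks are allowed for):

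- R = 10%, no region term: mean reported standard error 1.347 against a true SD of 1.290; level about 2.0%.
- R = 20%, no region term: 1.348 against 1.219; level about 1.1%.
- With region, the two agree (1.277 against 1.285; 1.204 against 1.209), and the level is 2.7% and 2.4%.
- Power without and with region: 93.2 and 94.6% at R = 10%; 94.2 and 97.0% at R = 20%.

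Levels rest on 8,000 runs each, a Monte Carlo standard error of √(0.025 × 0.975 / 8000) = 0.17 points. The simulation agrees with the formulas in direction and approximate size.

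**The case against.** The strongest reply is that R may be negligible. The model already adjusts for each home's baseline prevalence of the same outcome, so a stable regional difference in restraint use would appear at baseline and be largely absorbed. The Background attributes the marked variation to individual homes and their culture of care and does not mention region. The stated reason for stratifying is only that regional differences might matter. All of this stands: the size of the effect is unknown, and at R = 1% it hardly shows.

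Three stronger readings are tempting, and the article does not support them.

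- A reader might infer that the trial is underpowered or its test invalid. The estimate is unbiased, the error is on the conservative side, and the sample size takes no credit for region. At the stated SD of 6.0, 38 homes per group keep the planned 90% power.
- A reader might infer that the benefit of stratifying is lost. The estimate keeps it; only the reported standard error and the test fail to reflect it.
- A reader might set the powers with region against the 91.1% that applies when R = 0 and read off gains of about 1.4, 2.7 and 5.1 points at R = 5, 10 and 20%. That is the wrong comparator. Under stratified randomisation the power of the planned model rises with R too, so the gains are about 0.8, 1.6 and 2.8 points.

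The calculation applies to the cluster-level linear model. It does not carry over to the resident-level binary model with a random cluster effect, so no gain is claimed there.

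**Conclusion.** The point holds as a modest matter of efficiency and calibration. The omission is explicit and sits badly with the article's own reason for stratifying. If region explains 1 to 20% of the residual variance beyond baseline, the standard error is 0.5 to 11.8% too large, the nominal 2.5% test runs at about 2.4 down to 1.2%, and between 0.1 and 2.8 points of power go unused at 38 homes per group. The omission itself is certain. Its size rests on an assumed R and on 6.0 as the residual SD. Validity and planned power are not in question. The case for change is that including region costs almost nothing if region is irrelevant and makes the standard error match the design if it is not.

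**What to change.** Add region as a fixed effect (three indicators) to the list of independent variables in the primary cluster-level model, and fix this before any unblinded analysis so that the choice of model cannot depend on results. Add region to the resident-level and secondary-outcome mixed models as well, for consistency. The cost is one clause in the text and 3 degrees of freedom (110 to 107 at 38 homes per group), worth under 0.1 point of power if region explains nothing. The sample size need not change.

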##### Resident level

All of the residents living in the nursing homes and present on the day of data collection will be included. All of those newly admitted to clusters during follow-up and present on the day of follow-up data collection will also be included in the study. Newly admitted residents not present on the day of PR assessment will not be included.

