### Outcome measures

The primary outcome is the proportion of residents with at least one PR after twelve months. Data will be collected through direct observation at three measurement points: before randomisation (T_0_), after six months (T_1_) and after twelve months (T_2_). Observations at T_1_ and T_2_ will be performed by blinded research assistants. In contrast to our earlier study [1], observations will be performed only twice per day (morning and evening) instead of three times per day for reasons of feasibility.

Secondary outcomes are the residents’ quality of life and numbers of falls and fall-related fractures. The residents’ quality of life will be assessed using the German version [23] of the Quality of Life-Alzheimer’s Disease – QoL-AD [24, 25] at T_0_ and T_2_. This valid instrument has recently demonstrated its applicability and practicability in more than 2,000 people with dementia assessed in a European study [26]. For reasons of feasibility, a randomly chosen subgroup of 10 % of the residents will be selected. Proxy ratings will be done by nursing staff. Falls and fall-related fractures will be assessed by prospective documentation. In Germany, nursing homes are obliged to document this information.

Supported by the nurses, baseline data will be collected before randomisation for all residents living in the clusters. Here, characteristics of nursing homes and residents will be assessed including nurses’ proxy rating of residents’ cognitive status and challenging behaviour. The Dementia Screening Scale – DSS [27] will be used for assessing residents’ cognitive status. Challenging behaviour will be assessed using a modified German version of the Cohen-Mansfield Agitation Inventory – CMAI [28–30] which was already applied in previous studies [1, 5]. An abbreviated baseline assessment will be performed for residents admitted during the study period and present at the day of the follow-up data collection.

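### The secondary resident-level restraint model adjusts for a baseline value that residents admitted after T0 cannot have, so it drops outcomes the plan says it will use

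*Protocol article*

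**What the plan says.** All statements are in the protocol article.

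- **Who is included (Inclusion and exclusion criteria, Resident level).** "All of those newly admitted to clusters during follow-up and present on the day of follow-up data collection will also be included in the study". The resident sample is therefore an open cohort.
- **When PR is observed (Outcome measures).** T0 comes before randomisation, T1 at six months and T2 at twelve months. For later arrivals: "An abbreviated baseline assessment will be performed for residents admitted during the study period and present at the day of the follow-up data collection".
- **The model (Statistical analysis).** The article labels this analysis as secondary and gives its aim: "the time courses of the prevalence in the three groups will be investigated on resident level, adjusting for clusters and for repeated measurement". The response is the resident's binary PR status. "Fixed effects are treatment group, time, interaction of treatment and time, and the baseline value of PR". The home enters as a random effect, and repeated measurement is handled by a covariance pattern.
- **Missing data (same section).** The mixed models are said to draw on every available resident value and "do not exclude residents because of partially incomplete values". Also: "It is not planned to impute missing values".
- **For contrast, the primary model (same section).** It is a linear model on homes and adjusts for each home's baseline prevalence.

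**The concern.** A likelihood-based mixed model tolerates a missing response: a resident seen at T1 but not at T2 still contributes the T1 value. It does not tolerate a missing fixed-effect covariate. Without imputation, a record with no baseline PR value leaves the fit, even though its outcome was observed. Followed as written, the plan therefore includes later admissions in the study, observes their restraint status and then removes them from the resident-level model, while stating that the mixed models do not lose residents in this way.

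What is at stake is the population described. The primary analysis takes each home's twelve-month prevalence over the residents observed there, newcomers included. The resident-level model would cover only residents already observed at T0. If the programmes work differently for people admitted under the changed practice than for people already restrained at T0, the two analyses could disagree simply because they cover different residents.

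**Working it through.** **The plan's own figures.** Inputs from Sample size calculation: difference 5 points, SD 6.0, two-sided alpha 0.025, power 90%. The standardised difference is 5/6. A two-sample t-test needs 37.03 homes per group, rounded up to 38. Allowing 5% dropout, 38/0.95 = 40 per group; 3 x 40 = 120 homes; 120 x 90 = 10,800 residents. These reproduce. They concern the home-level primary analysis and are not in dispute.

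**The statements side by side.**
1. A resident admitted after T0 and present at T1 or T2 is in the study.
2. T0 precedes randomisation, so this resident has no T0 restraint value.
3. The model needs a baseline PR value on every record.
4. No value is imputed.
5. From 1 to 4, the record is dropped although its PR outcome was observed. That conflicts with using all available values without excluding residents for incomplete data.

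The abbreviated baseline assessment does not fill the gap. It is for newcomers present on the follow-up day. A PR status taken then is post-randomisation and would coincide with the outcome being modelled.

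**Check on a synthetic data set.** With 120 homes x 90 residents, about 30% of them without a baseline value, a logistic GEE (a stand-in for the planned mixed model) with the resident's baseline as covariate kept 7,591 of 10,800 records. All 3,209 later admissions were dropped (7,591 + 3,209 = 10,800).

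**Size of the loss.** The document gives no turnover rate. Let t be the share of T2 residents admitted after T0 (assumed, 10% to 40%), and suppose half of that turnover has occurred by T1 (also assumed).
- T2 observations lost = 10,800 x t.
- Share of T1 and T2 observations lost = (t + t/2)/2 = 0.75t.

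| t | T2 observations lost | Share of T1+T2 lost |
|---|---|---|
| 10% | 1,080 | 7.5% |
| 20% | 2,160 | 15% |
| 30% | 3,240 | 22.5% |
| 40% | 4,320 | 30% |

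Residents absent on the T0 day would add to these counts.

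**What the change of population can do.** These effects are invented for illustration, on the prevalence scale, with t = 30%.
- 3 points in residents present at T0 and 8 in newcomers: whole-home effect 0.7 x 3 + 0.3 x 8 = 4.5, against 3 in the restricted sample.
- 6 and 2 points: 0.7 x 6 + 0.3 x 2 = 4.8, against 6.
- 5 points in both groups: 5 either way.

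The direction of any discrepancy cannot be known in advance, and there may be none.

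**The case against.** **The baseline value may be the home's.** The text does not say whose baseline it is. If it is the home's T0 prevalence, as in the primary model, every resident has one and the problem disappears. This is the best defence. Against it, the model is at resident level with a binary PR response, and the article speaks of prevalence when it means the home. The resident's own value is the more natural reading. If the home's value was intended, the sentence still needs to say so.

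**It is a secondary analysis in a condensed article.** Both are true, and the first limits the severity. The second does not remove the point: the article has itself fixed the covariate, ruled out imputation and claimed no exclusions, and those statements conflict.

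**Stronger readings that a reader might infer, and that the document does not support.**
- *T0 is both response and covariate, so the treatment effect is distorted.* The three time points are listed in the sentence on descriptive statistics; the model sentence speaks only of time courses. A baseline-adjusted model ordinarily has T1 and T2 as responses. The option of dropping the treatment-by-time term also fits that better, since with T0 as a response that term carries the treatment effect. Nor does simulation establish bias. In a pooled logistic fit, which is not the planned model, adding T0 rows moved the T2 log odds ratio from -0.255 to -0.336. The simulated conditional effect was -0.35, and odds ratios shift with what is conditioned on. The ratio of estimate to its empirical SD hardly changed (0.255/0.083 = 3.07; 0.336/0.110 = 3.05).
- *Only long-stay survivors remain.* A resident seen at T0 and T1 who leaves before T2 still contributes at T1.
- *The comparisons of falls, fractures and quality of life share the defect.* The article refers back to the restraint model but names only the adjustment for clusters and repeated measurements. Carry-over of the baseline covariate is possible, not stated.

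**Conclusion.** The inconsistency stands for the secondary resident-level PR model, on the reading that the covariate is the resident's own T0 status. It follows from the stated rules and does not depend on any turnover figure; only its size does. Under the assumed 10% to 40% of T2 residents admitted after T0, about 1,080 to 4,320 of 10,800 T2 observations would be lost, and the model would describe a different population from the primary analysis. Whether the estimated effect would change is unknown, because that depends on whether newcomers respond differently. The home-level primary test, its significance level and the 120-home sample size are untouched. Severity is moderate.

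**What to change.** State whose baseline is meant, and make the covariate one that every included resident has. Either of these would do:

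1. **Home baseline.** Replace the resident's own baseline PR with the home's T0 prevalence, with T1 and T2 as the responses. Every resident, newcomers included, then has a covariate value, and the adjustment matches the primary model.
2. **T0 as a response.** Model T0, T1 and T2 without the baseline covariate, with the arms constrained equal at T0. The treatment-by-time term must then stay in the model, so the option to drop it should be withdrawn for this version.

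A model with the resident's own T0 status can be kept as a sensitivity analysis, labelled as restricted to the T0 cohort. If the mixed models for quality of life, falls and fractures also carry a resident-level baseline covariate, make the same change there; if they do not, say so.

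The cost is a few sentences in the analysis plan. No new data are needed, and the sample size does not change.
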